**Fig. 1 Fig1:**
[figure not shown]
Schedule of enrollment, intervention, and assessments (SPIRIT Figure)

### Randomization

Following baseline survey completion, AYAs are randomized 1:1 to the intervention or the control arm, with strata defined by age group (12–17 vs. 18–25 years) and study site. The randomization was constructed by the study statistician using a permuted blocks scheme with randomly varying block sizes. Study staff administer randomization assignments using REDCap [57] and maintain a randomization log; staff do not have access to the random allocation sequence. Blinding of study staff or participants is not feasible or practical given the nature of the intervention; however, study statisticians will be blinded to group assignment for data analysis.

### Intervention

#### Usual care

Participants randomized to both arms receive psychosocial usual care. At both sites, this includes an assigned social worker who conducts a comprehensive assessment at diagnosis and provides additional ad hoc services throughout treatment, with professional psychology services available upon family request or care team referral.

#### PRISM-SN intervention

Participants randomized to the intervention arm receive the PRISM-SN program in addition to UC. PRISM-SN includes an introductory meeting, five core modules (four standard PRISM modules + new social needs [SN] module), and a final family meeting. Each module is delivered as a single 30–60-min session; 1:1, in person or via videoconference; approximately 1–2 weeks apart.

PRISM-SN is delivered by trained “coaches” with a bachelor’s degree or higher who complete a standardized intervention training (i.e., 8 h of supervised didactics, role-playing scenarios, recognizing signs of psychological distress or risks of harm). Coach supervision and fidelity monitoring are conducted by the PI. Fidelity is assessed for the first 5 sessions delivered by each coach and 1 in 5 randomly selected sessions thereafter using a standardized scoring system developed for the PRISM program [28]. Coach supervision includes weekly study team check-ins; monthly group supervision meetings to provide feedback and discuss emergent concerns; and re-training as needed to address fidelity concerns.

Intervention content is described in Table 1. The introductory meeting includes discussion of the concept of resilience and review of participants’ “toolkit”, or existing skills for managing stress. Next, through each module, AYAs learn “resilience resources” or skills associated with wellbeing. Skills are taught using AYA-specific example scenarios as behavioral models and practiced in-vivo using a participant-generated example. As described elsewhere [51], the social needs module (i.e., Module 5: Connecting with Others) includes two new skills focused on identifying support and navigating relationship challenges. In the final session, participants review what was learned through the program, how to integrate new skills into their “toolkit”, and have the option to invite a parent or support person to join. To practice skills between sessions, participants receive paper “cheat-sheets” corresponding with each session and are invited to download the PRISM mobile app. App content mirrors paper cheat-sheets for all sessions except “Connecting with Others”, for which mobile app content is not yet available.

**Table 1 Tab1:** The Promoting Resilience in Stress Management–Social Needs (PRISM-SN) Intervention

Session	Skill(s) and content	Delivery
Introduction + PRISM 1: Managing Stress^+^	Introducing resilience “toolkit”; Deep-breathing, mindfulness strategies	1:1
PRISM 2: Catching Negative Thoughts^+^	Recognizing and reframing negative self-talk	
PRISM 3: Setting Goals^+^	Setting SMART goals	
PRISM 4: Meaning Making^+^	Identify meaning, purpose from cancer experience	
PRISM 5: Connecting with Others^*^	Identifying support, navigating relational challenges	
Family meeting	Reviewing what was learned, discussing how loved ones can help	1:1 or group

*Note*: ^+^Standard PRISM module

^*^New social needs (SN) module

Various strategies are employed to promote uptake, adherence, and retention. Sessions may be delivered in-person or remotely based on participant preference. In-person sessions are scheduled in tandem with oncology clinic visits or inpatient stays and do not require additional hospital visits. All sessions are scheduled in advance, and participants receive reminder calls or emails one day prior. For participants with scheduling challenges or limited availability, two modules may be delivered within a single session. Intervention arm participants who request to discontinue participation are given the option to stop intervention sessions and remain in the study (and thus remain eligible to complete the follow-up survey) or withdraw from the research entirely. Any reasons provided for discontinuing sessions are documented.

### Outcomes

#### Feasibility and acceptability outcomes

Our first aim is to establish feasibility and acceptability of the PRISM-SN program. Our *a priori* feasibility outcomes include: (a) *uptake*, calculated as the proportion of AYAs enrolled out of total AYAs approached and (b) *retention*, calculated as the proportion of AYAs who remain in the study at 12 weeks out of total AYAs enrolled. PRISM-SN will be considered feasible if uptake is ≥ 70% and retention is ≥ 70%. We will also examine additional feasibility outcomes relevant to intervention delivery and adherence, including the number of sessions completed, session format and frequency, intervention length, and fidelity. *Acceptability *will be determined via the patient-reported Acceptability of Intervention Measure [58] at 12 weeks. This validated instrument includes 4 items such as “[program] meets my approval,” scored 1–5, with higher average scores reflecting more acceptability. PRISM-SN will be acceptable if ≥ 80% of AYAs on the intervention arm have an average score of ≥ 4 on this measure.

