## Objectives and study design

This article describes the protocol of a pilot randomized-controlled trial (RCT) of the Promoting Resilience in Stress Management–Social Needs (PRISM-SN) adapted intervention among AYAs newly diagnosed with cancer**.** Our objectives are to assess the following: (1) feasibility, quantified via uptake, retention, and intervention acceptability; and (2) proof-of-concept, measured via minimal important difference on patient-reported outcomes (PROs) including SRCE (primary PRO of interest), social support, quality of life, hope, resilience, anxiety, and depression. For this pilot, parallel-group randomized trial, participants are randomized 1:1 to psychosocial usual care (UC, “control”) or PRISM-SN + UC (“intervention”) and complete PRO surveys at baseline and 12-week follow-up. We selected a pilot trial design with UC as our comparator to establish feasibility of delivering the PRISM-SN program in the context of a randomized trial and determine whether there is a signal of change in psychosocial outcomes in response to PRISM-SN compared to current standards of care. This protocol is reported following SPIRIT guidelines [55] adapted based on the CONSORT extension to pilot and feasibility trials [56] (Additional file 1).

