## Discussion

This paper describes the protocol for a pilot randomized trial to demonstrate feasibility and proof-of-concept for the Promoting Resilience in Stress Management–Social Needs (PRISM-SN) intervention. PRISM-SN is an adaptation of an established psychosocial program [28, 43] including a new component designed to enhance social connection for AYAs newly diagnosed with cancer [51]. Anticipated outcomes from this study include feasibility, measured by uptake, retention, and intervention acceptability, and proof-of-concept, determined based on improvements in patient-reported social outcomes at 12-week follow-up.

This study has important strengths related to the intervention and study design. Leveraging an already established and successful program [43, 45, 46, 70], PRISM-SN applies a novel, developmentally informed, skills-based approach to target social connection, a previously unmet need for AYAs with cancer. In addition, the two-site pilot randomized trial design has the potential to provide stronger evidence of feasibility compared to smaller single-arm studies. This study will demonstrate the feasibility of delivering the PRISM-SN program; of recruiting and retaining AYAs in both the UC and intervention trial arms; and of implementing this protocol at multiple national sites. In addition, feasibility outcomes from this study will inform benchmarks for uptake, retention, intervention adherence, and data completion for a subsequent multi-site efficacy trial.

Limitations of this protocol should also be noted. First, generalizability may be limited by study sites and the patient populations they serve. Both sites are academic, pediatric-based AYA oncology centers who serve patient populations with limited racial and ethnic diversity. Subsequent trials of this program will need to recruit larger, more diverse samples and determine whether this protocol is feasible at community-based or adult AYA cancer centers. Second, PRISM-SN is only available in English; translation to other languages is an important future direction. Third, this pilot trial will not be powered to test whether delivery adaptations to promote accessibility (i.e., in-person vs. virtual sessions, combining modules) affect response to the program.

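### The rule that declares PRISM-SN feasible pools retention over both arms and omits acceptability, so it can be met when intervention-arm retention is well below 70%

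*Protocol article*

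**What the plan says.** The protocol article, under Feasibility and acceptability outcomes, defines uptake as "calculated as the proportion of AYAs enrolled out of total AYAs approached" and retention as "calculated as the proportion of AYAs who remain in the study at 12 weeks out of total AYAs enrolled". The decision sentence follows: "PRISM-SN will be considered feasible if uptake is ≥ 70% and retention is ≥ 70" (both per cent). Neither proportion is split by arm or site. Sessions completed, their format and frequency, intervention length and fidelity are additional outcomes without a threshold. Acceptability has its own criterion in the same section: at least 80% of the intervention arm with a mean score of 4 or more at 12 weeks. The decision sentence does not mention it.

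Other sections bear on the same conclusion:

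- Objectives and study design describes "feasibility, quantified via uptake, retention, and intervention acceptability". The Methods part of the Abstract and the opening of the Discussion list the same three components.
- PRISM-SN intervention says that participants who wish to discontinue "are given the option to stop intervention sessions and remain in the study".
- The Discussion says the study will show that the programme can feasibly be delivered, and the feasibility "of recruiting and retaining AYAs in both the UC and intervention trial arms; and of implementing this protocol at multiple national sites".
- Data analysis and sample size plans 100 recruited and 70 evaluable (35 per arm) at 30% attrition, with margins of error of ±11% at a rate of 70% and ±9% at 80%.

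**The concern.** The conclusion drawn from the rule is about PRISM-SN, but neither input is specific to PRISM-SN. Uptake is settled before randomization. Retention averages an arm that receives the programme with an arm that does not. Good retention on usual care can therefore offset poor retention on PRISM-SN, and the rule will still declare the programme feasible. Delivery does not enter the rule at all, although feasible delivery is one of the conclusions the Discussion announces.

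The second problem is one of consistency. Three places make acceptability a component of feasibility; the only sentence that states a decision leaves it out. If uptake and retention pass and acceptability fails, the article gives two answers.

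What is at stake is the pilot's first objective, and with it the case for a larger multi-site trial that would rely on these retention and adherence figures.

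**Working it through.** **1. The article's own figures.** The 95% half-width is 1.96 × √[p(1 − p)/n].

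- p = 0.70, n = 70: 10.7 points (stated ±11%).
- p = 0.80, n = 70: 9.4 points (stated ±9%).
- 70/(1 − 0.30) = 100 to recruit.

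All reproduce. The point does not rest on a sample-size error.

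**2. What the pooled rule allows.** With 100 enrolled and 1:1 allocation, take 50 per arm, ignoring any loss before randomization. The retention criterion is met when the two arms together retain 70.

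| Usual care retained | Fewest on PRISM-SN that still meets the rule |
|---|---|
| 50/50 (100%) | 20/50 (40%) |
| 45/50 (90%) | 25/50 (50%) |
| 40/50 (80%) | 30/50 (60%) |
| 35/50 (70%) | 35/50 (70%) |

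**3. How often the two rules disagree.** Retention is treated as two independent Binomial(50, p) counts and enumerated exactly. The pooled rule needs at least 70 of 100; the same benchmark within the intervention arm needs at least 35 of 50. The true rates are assumptions, because the article gives none by arm.

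| True retention, usual care / PRISM-SN | Pooled rule passes | Intervention-arm rule passes |
|---|---|---|
| 70% / 70% | 0.55 | 0.57 |
| 80% / 60% | 0.55 | 0.10 |
| 90% / 60% | 0.91 | 0.10 |
| 90% / 50% | 0.55 | 0.003 |

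When both arms sit at 70% the two rules behave almost alike. They part when retention is worse on PRISM-SN.

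**4. Sites.** The site split is not given. If the larger site (or either site, at 50/50) retains 90%, the pooled 70% is met when the other retains (70 − 45)/50 = 50% at a 50/50 split, (70 − 54)/40 = 40% at 60/40, or (70 − 63)/30 = 23% at 70/30.

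**5. Acceptability.** In the 45/50 and 25/50 case, if the acceptability denominator is everyone randomized to PRISM-SN and only retained participants respond, at most 25/50 = 50% can score 4 or more, so the 80% criterion fails. By the decision sentence the trial is feasible; by the three-part definition in the Objectives it is not. If the denominator is responders only, 20 of 25 = 80% would pass, and acceptability would not reveal the loss.

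**6. Precision of an intervention-arm benchmark.** At p = 0.70: n = 50 gives ±12.7 points; n = 100 gives ±9.0 points.

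**The case against.** The strongest reply is that retention in a trial and adherence to an intervention are different things. Keeping those who stop sessions in follow-up is right for an intention-to-treat analysis, and counting them as retained is not an error. Adherence and fidelity are measured separately, and the article says the pilot will inform adherence benchmarks for a later trial, so setting none now is a coherent choice. This stands. It means the Discussion's delivery claim should be a descriptive one unless a benchmark is added; it does not make the retention definition wrong.

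Second, acceptability is specific to the intervention arm and gives some protection. It does, but it is outside the decision sentence, and its force depends on the denominator.

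Third, the arm rates are invented, and the 45/25 example lands exactly on the threshold. That is fair. Retention could even be better on PRISM-SN, where coaches keep contact. The example shows what the rule permits, not what is expected. Poorer retention on PRISM-SN is nevertheless plausible, since only that arm is asked for five modules of 30–60 minutes and a final family meeting.

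A reader might also infer stronger faults that the article does not support:

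- Uptake should have been split by arm. Consent comes before randomization, so it cannot be.
- An enrolled denominator flatters retention. If it includes people lost before randomization, it makes the criterion stricter.
- Retained status need not involve the 12-week survey, and sessions are the wrong unit because "two modules may be delivered within a single session". These are operational details that an article commonly leaves to the full protocol, and its list of delivery outcomes is not exhaustive.

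**Conclusion.** The point holds in a limited form. The article fixes a complete decision rule, and that rule can declare PRISM-SN feasible with intervention-arm retention of 60%, 50% or even 40%, depending on usual care. Under assumed true retention of 90% and 50% it passes with probability 0.55, against 0.003 for the same benchmark applied to the intervention arm. These figures assume 50 per arm and illustrative rates. The omission of acceptability from the decision sentence is an inconsistency that needs no assumption.

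It would go too far to infer that the trial cannot support any feasibility conclusion, or that delivery is likely to fail unnoticed. Arm, site, session and fidelity data will be available and can be reported. What falls short is the prespecified rule as the basis for claiming feasible delivery and feasible retention in both arms.

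**What to change.** Under Feasibility and acceptability outcomes:

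1. Keep uptake pooled over arms.
2. Apply the existing ≥ 70% retention benchmark to the intervention arm, and report retention for usual care and for each site beside it.
3. State whether the ≥ 80% acceptability criterion is required for the feasibility conclusion, in line with the Abstract and the Objectives.
4. Either base the claim of feasible delivery on a module-completion benchmark that the sponsor chooses and prespecifies, or word that claim in the Discussion as descriptive. The article gives no basis for a particular threshold, so none is proposed here.

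No new data are needed. The main cost is precision: ±12.7 points for the intervention arm, instead of ±9.0 for all enrolled or the article's ±11 for 70 evaluable. Because the criteria are called a priori and recruitment is described in the present tense, the change should be a dated amendment made before retention by arm is examined.

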### Data analysis and sample size

Conservatively assuming 30% attrition due to illness, death, or dropout, we anticipate recruiting 100 AYAs over 2 years, with an evaluable sample of 70 (*N* = 35 per arm). This sample size will provide a margin of error ± 11% at 95% confidence for an estimated rate of 70%; for a rate of 80%, the margin of error is ± 9% at 95% confidence. This pilot trial is not powered to detect efficacy; data will be used to demonstrate intervention feasibility and proof-of-concept and inform the design of future larger randomized trials including benchmarks for accrual, retention, and intervention adherence.

Primary statistical analyses will be conducted on an intention-to-treat basis to avoid confounding by non-random participant attrition. To determine feasibility and acceptability (Study Objective 1), benchmark proportions and descriptive statistics will be used to examine uptake and retention rates and AIM scores. To determine proof-of-concept (Study Objective 2), demographics, clinical characteristics, and PRO items will be summarized at each time point using descriptive statistics: frequencies and proportions for categorical variables, means and standard deviations for continuous variables, or the median and interquartile range if the distribution is markedly skewed. Categorical outcomes will be compared between arms using the chi-squared test, and continuous outcomes will be compared using two-sample *t*-tests. In addition, covariate-adjusted linear regression models will be used to compare PROs between study arms, in which study arm is the predictor of interest and the stratification factors, site and age, are the covariates. For PROs without an established minimal clinically important difference (MCID), we will define minimal important differences as ½ standard deviation based on comparison samples [69].

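### The acceptability benchmark is worded over the whole intervention arm, which does not fit the planned attrition; the respondent base that the plan seems to intend is open to attrition bias and should be named

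*Protocol article*

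**What the plan says.** In the protocol article, Feasibility and acceptability outcomes, acceptability "will be determined via the patient-reported Acceptability of Intervention Measure" at 12 weeks. The program is to be called acceptable if at least 80% "of AYAs on the intervention arm have an average score of" 4 or more. The same section defines uptake over those approached and retention over those enrolled, each with a 70% threshold.

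Data analysis and sample size gives the analysis basis: "Primary statistical analyses will be conducted on an intention-to-treat basis to avoid confounding by non-random participant attrition". For the first objective, "benchmark proportions and descriptive statistics will be used to examine uptake and retention rates and AIM scores". The sample size rests on "assuming 30% attrition due to illness, death, or dropout, we anticipate recruiting 100 AYAs over 2 years, with an evaluable sample of 70", which is 35 per arm, and margins of error of ±11% for a rate of 70% and ±9% for a rate of 80% are quoted. Randomization gives 1:1 allocation.

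Under PRISM-SN intervention, participants who want to discontinue may stop sessions but stay in the study and answer the follow-up survey, or may withdraw altogether.

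**The concern.** The benchmark is a pass/fail rule with a stated base, the AYAs on the intervention arm. Taken together with the intention-to-treat sentence, that base is everyone randomized to PRISM-SN. The score exists only for those who answer at 12 weeks, and the plan allows for 30% who will not. If people without a score cannot count towards the 80%, the bar sits above what the planned number of respondents can deliver.

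The other reading, a base of 12-week respondents, removes that conflict. But it conditions on staying in the study, and missing scores may be related to how the program was received. That is the non-random attrition that the intention-to-treat sentence is meant to guard against.

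At stake is one of the trial's few pre-set thresholds and part of its first aim. The same data can pass on one base and fail on the other, and the text does not settle which base decides.

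**Working it through.** **Inputs.** Recruited: 100; attrition: 30%; evaluable: 70 in total and 35 per arm (Data analysis and sample size). Allocation: 1:1 (Randomization). Benchmarks: acceptability at least 80%, retention at least 70% (Feasibility and acceptability outcomes).

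**Assumptions.** All 100 are randomized, so the intervention arm has about 100/2 = 50. Attrition is equal in the two arms. An evaluable participant has a 12-week AIM score.

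**1. The plan's own figures reproduce.**
- Recruitment: 70/(1 − 0.30) = 100.
- Margin at 70%: 1.96 × √(0.70 × 0.30/70) = 10.7%, stated as ±11%.
- Margin at 80%: 1.96 × √(0.80 × 0.20/70) = 9.4%, stated as ±9%.

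Both margins use n = 70, the evaluable sample of both arms. The only 80% benchmark concerns the intervention arm alone. With n = 35 the margin is 1.96 × √(0.80 × 0.20/35) = 13.3%.

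**2. Base of all randomized to PRISM-SN, missing scores not counted as accepting.**
- Needed: 0.80 × 50 = 40 participants scoring 4 or more.
- Available: 35 with a score, so the ceiling is 35/50 = 70%.

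| Arm retention | With a score | Highest possible rate | Share of respondents who must score ≥4 |
|---|---|---|---|
| 70% | 35 | 70% | not attainable |
| 80% | 40 | 80% | 40/40 = 100% |
| 90% | 45 | 90% | 40/45 = 89% |
| 100% | 50 | 100% | 40/50 = 80% |

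Arm retention from 70% to under 80% therefore meets the level called feasible and leaves the acceptability bar out of reach. If 70% is each participant's chance of being retained, rather than a fixed count, the binomial probability of at least 40 of 50 being retained is 7.9%. On this base the benchmark could be met at most that often, even if every respondent approved.

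**3. Base of 12-week respondents.**
- Needed: 0.80 × 35 = 28. Then 28/35 = 80%, a pass.
- Over all 50 randomized, the 15 missing give a worst case of 28/50 = 56% and a best case of (28 + 15)/50 = 86%.

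**The case against.** The strongest reply is that the 70% ceiling rests on a rule that the document does not contain. Intention-to-treat fixes the arm in which people are analysed. It does not say that a missing score is a failure, and an analysis with imputation would have no such ceiling. This stands.

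The text also leans towards respondents. Having an average score presupposes a score, the retention rule names its all-enrolled base while the acceptability rule does not, and the ±9% for an 80% rate is computed on the evaluable sample. The 30% is introduced with "Conservatively assuming 30% attrition due to illness, death, or dropout", so it is a planning allowance, and at 80% arm retention or more the bar can be reached. A reader might infer that the trial is bound to fail its own benchmark, or that the two benchmarks contradict each other outright. The documents support neither: both hold only on the all-randomized base with missing scores counted against the program.

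A reader might also infer that a respondent base counts only people who finished and liked the program. The documents do not support that either. Those who stop sessions may still answer the survey, attrition is put down to illness, death or dropout, and retention and sessions completed are reported separately. What remains is possible upward bias from those who withdraw fully or cannot be reached. Its size cannot be derived from the document.

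Finally, missing-data handling for a descriptive proportion is usually left to a statistical analysis plan, which is not at hand. That is fair for the method. It does not cover a decision rule that is stated here, on a base that does not fit the figures given two sections later.

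**Conclusion.** The point holds in a limited form. As worded, the acceptability rule conflicts with the plan's own figures: at most 70% of the arm can qualify against a bar of 80%, if the base is all randomized, attrition is 30% in that arm and missing scores do not count as accepting. If respondents are the intended base, as the precision statement suggests, the rule is workable. A pass at 28/35 would then be compatible with anything from 56% to 86% of the arm accepting.

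The severity is moderate. Objective 1 is descriptive, the trial is a pilot, and naming the base removes the conflict. It should be done before the data are analysed, because the choice can turn a pass into a fail.

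**What to change.** 1. State that the benchmark is judged among intervention-arm participants with a 12-week AIM score, and that this figure decides.
2. Beside it, report the AIM response rate and the proportion of all randomized to PRISM-SN, with worst-case and best-case bounds for missing scores.
3. Qualify the acceptability conclusion if the bounds straddle 80%.
4. Give the precision for the 80% benchmark on the intervention arm (about ±13% at n = 35).
5. Optionally, offer the four-item AIM when a participant stops sessions, where any reasons given are already documented. Use it only as a supplementary sensitivity value and do not mix it into the 12-week benchmark.

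The cost of items 1 to 4 is wording and one extra line in a results table; item 5 adds a short form at an existing contact. The downside is that a second, less favourable figure is reported. With 35 of 50 responding, any pass would also carry the qualification: the worst case cannot exceed 35/50 = 70%, and the best case is at least 43/50 = 86%. It falls away only when at least 40 of the 50 are known to accept.
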